### Objectives

The objectives of the study are to evaluate the placed single dental implant in the cleft region for clinical and radiological parameters 3 months after dental implant placement; evaluate the placed single dental implant in the cleft region for clinical and radiological parameters 9 months after dental implant placement (6 months after definitive prosthesis); and evaluate and compare the placed single dental implant in the cleft region for clinical and radiological parameters 3 months and 9 months after dental implant placement.

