### Operative Assessment

All patients with a single tooth missing in the cleft area will undergo preoperative screening using an orthopantogram (OPG) supplemented with an intraoral periapical radiograph (IOPAR) and bone mapping to determine the need for tertiary grafting. Prior to tertiary grafting, all patients will have the Oral Hygiene Index-Simplified (OHI-S) recorded followed by conduction of oral prophylaxis [11]. Following standard procedure guidelines, bone grafting will be done by a single operator using either an autologous symphyseal bone graft or iliac bone graft, depending on the amount of bone required [12-14]. Before proceeding with implant surgery, the OHI-S will be re-assessed and compared with the previously recorded observations. This will help to determine the patients’ attitudes towards oral health and their motivation towards maintaining oral hygiene. Cone beam computed tomography (CBCT) will be recorded 3-6 months after grafting to evaluate the integration of the grafted bone and plan implant placement. Before proceeding with implant surgery, the OHI-S will be re-assessed and compared with the previously recorded observations. In all patients, titanium dental implants (TitanGrade 4, blasted etched implant surface, Bredent GmbH Co, Senden, Germany) will be placed following a one-stage protocol. Additional bone graft material will be used to ensure complete bony coverage of the dental implant surface, if required. The implants will be placed slightly subcrestally, and the primary implant stability will be clinically evaluated by measuring implant stability quotient (ISQ) values using a Penguin^RFA^ device. The obtained values will be interpreted as follows [15]: ISQ ≥70: high initial stability and suitable for immediate loading; ISQ 55-70: moderate stability; ISQ ≤55: low/questionable stability and not suitable for immediate loading. Following the immediate loading protocol, all implants will be loaded with a provisional prosthesis made of autopolymerizing resin (ie, a provisional prosthesis will be placed within 7 days of dental implant placement) [16]. All patients will be educated about oral hygiene habits to ensure proper care of the placed implant and prosthesis along with use of a 0.12% chlorhexidine rinse for 30 seconds at least twice a day [17].

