### Follow-Up

All patients will undergo 2 clinical follow ups, 3 months and 9 months after implant placement. At the first follow-up after a period of 3 months following immediate implant loading, the provisional prosthesis will be removed, and clinical and radiological parameters will be measured. Clinical parameters will include probing depth, bleeding on probing, suppuration, pain or tenderness in the implant area, and implant stability using ISQ values. The implant will then be loaded with a definitive prosthesis, and a CBCT will be recorded. A second follow-up will be performed after 6 months of definitive prosthesis placement (ie, a cumulative period of 9 months following implant placement), and all parameters will be assessed as stated previously. At the end of the treatment, all patients will be asked to complete a quality of life (QoL) assessment questionnaire to determine the patient’s perspective before and after dental implant treatment.

CBCT recordings will be done using a small sized field of view of approximately 50 mm in diameter, which has an effective dose of approximately 54µSv [18].

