## Results

IBM SPSS version 23 and R 4.0.3 will be used for statistical analysis. Results will be aimed at determining the clinical and radiographic success of dental implants in patients with a nonsyndromic alveolar cleft. The Cox model of analysis will be used to determine the shared frailty of dental implants in case of bilateral cleft cases. The Kolmogrov-Smirnov test will be applied to determine the normality of the data. Depending on the data distribution, *t* tests, Wilcoxon tests, and chi-square tests will be utilized to determine statistical significance of clinical and radiological parameters assessed at 3 months and 9 months post implant placement. Binary logistic analysis will be done to compute the predictors of the outcome. CBCTs recorded after dental implant placement will be quantitatively compared to determine the presence of any significant variation in the marginal bone levels. Qualitative assessments of the radiographs will be done to determine the presence of periapical pathology and any other abnormal radiographic findings. Intra- and inter-observer variability in radiographic assessments will be evaluated by using the Kappa statistic. Statistical significance will be set at *P*<.05.

Implant success will be defined based on the guidelines given by Misch et al [19] in the Pisa, Italy Consensus and as presented in the patient record sheet. Statistical comments on the implant survival rate will be given by calculation of a life table analysis.

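### Bone level and ISQ are compared only between 3 and 9 months, so change during the provisional, immediately loaded phase is not estimated

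*Protocol article*

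**What the plan says.** All places are in the protocol article.

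- **Loading.** Operative Assessment states that "a provisional prosthesis will be placed within 7 days of dental implant placement".
- **Visits.** Follow-Up states: "All patients will undergo 2 clinical follow ups, 3 months and 9 months after implant placement". At the first, "the provisional prosthesis will be removed, and clinical and radiological parameters will be measured". Then: "The implant will then be loaded with a definitive prosthesis, and a CBCT will be recorded". For the later visit, "A second follow-up will be performed after 6 months of definitive prosthesis placement", with the same parameters assessed again.
- **Measurement at surgery.** Operative Assessment says: "The implants will be placed slightly subcrestally, and the primary implant stability will be clinically evaluated by measuring implant stability quotient (ISQ) values". It names no radiograph at that moment and gives no figure for depth. The only earlier CBCT is the planning scan, 3 to 6 months after grafting.
- **Comparison.** The third objective is to "evaluate and compare the placed single dental implant in the cleft region for clinical and radiological parameters 3 months and 9 months" after placement. Results applies the significance tests to parameters at those two times and adds that "CBCTs recorded after dental implant placement will be quantitatively compared to determine the presence of any significant variation in the marginal bone levels".

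**The concern.** The aim is the clinical and radiographic success of immediately loaded implants. The Introduction describes conventional practice as 3 to 6 months of healing before loading. Months 0 to 3 are therefore when this treatment departs from convention, and the Scope section claims that early function will itself prevent bone loss. A comparison that starts at month 3 cannot test that claim. Any bone lost earlier is already contained in the 3-month value and drops out of the difference. The same holds for ISQ, although a placement value exists. A bone level at insertion that was never recorded cannot be recovered later by an analysis plan.

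**Working it through.** **Step 1: set the schedules side by side.**

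| Time | Prosthesis | Bone imaging named in the text | ISQ |
|---|---|---|---|
| Before placement, 3–6 months after grafting | none | planning CBCT | – |
| Placement (month 0) | provisional within 7 days | none named | yes |
| Month 3 | provisional removed, definitive fitted | CBCT | yes |
| Month 9 | definitive for 6 months | CBCT (implied: all parameters repeated) | yes |

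The compared interval is months 3 to 9. The provisional-loading interval runs from within 7 days of placement to month 3. The two do not overlap, and the uncovered part is 3/9, one third of follow-up.

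**Step 2: what the difference estimates.** Let L1 be bone loss from month 0 to 3 and L2 loss from month 3 to 9.

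- Total loss = L1 + L2.
- The planned comparison estimates L2 only.
- Share missed = L1 / (L1 + L2).

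The documents give no values for L1 or L2. The following are assumptions, for illustration only.

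| L1 (mm) | L2 (mm) | Total (mm) | Seen (mm) | Share missed |
|---|---|---|---|---|
| 0 | 0.1–0.5 | 0.1–0.5 | 0.1–0.5 | 0% |
| 0.5 | 0.5 | 1.0 | 0.5 | 50% |
| 1.0 | 0.3 | 1.3 | 0.3 | 77% |
| 1.5 | 0.1 | 1.6 | 0.1 | 94% |

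If there is no early loss, nothing is missed, but the comparison could not show that this was so.

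**Step 3: can the planning CBCT serve as baseline?** Not as the plan stands. It predates the implant, bone may be added at surgery (Operative Assessment), and Results restricts the comparison to scans taken after placement.

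**Step 4: what the 3-month scan can show on its own.** Let d be the depth of the implant shoulder below the crest at insertion. The text implies d > 0 but gives no value.

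- Bone at distance x below the shoulder at month 3: loss = d + x, so loss is at least x.
- Bone still at distance y above the shoulder: loss = d − y, which is unknown without d and can be at most d.

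The 3-month level thus gives a lower bound on early loss if it is reported relative to the shoulder. What is missing is d.

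**Step 5: ISQ.** Values exist at months 0, 3 and 9. The changes 0–3 and 0–9 can be calculated from data already collected, but the stated tests name only 3 and 9 months.

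**Step 6: sample size.** The stated 28 rests on the success proportion: 1.96² × 0.95 × 0.05 / 0.08² = 28.5, and 28/0.95 = 29.5, giving 30. It reproduces to within rounding and does not depend on bone change, so this point leaves it untouched.

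**The case against.** The strongest reply has four parts.

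1. **Unseen material.** Figure 1 and the patient record sheet are not available here. The record sheet has a surgical section on implant placement, and the sentence on comparing CBCTs gives no times. A placement radiograph or an insertion depth may already be recorded. This stands as a limit on certainty. It would make the fix easier but would not settle the point, because the objectives and the stated tests would still compare 3 with 9 months.

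2. **Early loss is not invisible.** A reader might infer that bone lost before month 3 vanishes from the trial. The documents do not support that. The first objective evaluates radiological parameters at 3 months in their own right. Subcrestal placement with full bony coverage also means that bone below the shoulder at that visit is visible loss of at least that height. This stands.

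3. **Success is not the CBCT comparison.** A reader might infer that an implant with early loss that then stabilised would count as a success. That does not follow. Results defines success separately, by consensus criteria set out in the record sheet, and clinical signs and survival are also assessed. How those criteria take their bone-loss baseline cannot be seen here.

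4. **Months 3 to 9 still count.** A reader might infer that the whole exposure of interest is left out. It is not. These implants remain immediately loaded implants after month 3, and the objectives include month 9 explicitly. Only the provisional phase is left out of the change estimate.

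**Conclusion.** The point holds in limited form. On the text shown, the planned bone-level and ISQ comparisons run from 3 to 9 months, and no bone level at insertion is named. Change over the first 3 of 9 months, the provisional phase, is not estimated. The 3-to-9-month difference alone therefore cannot show whether bone was lost early under immediate loading. The 3-month evaluation and the success criteria may still detect marked loss, and the 3-to-9-month change remains informative. Survival, clinical signs and sample size are unaffected.

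The size in millimetres is unknown, and the 0% to 94% range rests wholly on assumed losses. The conclusion also assumes that neither the figure nor the record sheet already provides a bone baseline at placement that feeds the analysis. Because the improvement is cheap and a missing baseline cannot be recovered afterwards, the change should be made before implants are placed.

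**What to change.** 1. Analyse ISQ change from the placement value to 3 and to 9 months. The data are already collected, so this costs only wording.
2. Report bone level relative to the implant shoulder at 3 months and at 9 months, not only the difference between them. This uses the planned scans.
3. Record the depth of the implant shoulder relative to the crest at insertion, at fixed sites, on the surgical section of the record sheet. If a placement radiograph already exists in the figure or record sheet, name it as the baseline instead, in Objectives, Follow-Up and Results.
4. Make bone change from insertion to 3 and to 9 months the bone-loss measure for the success criteria, and keep the 3-to-9-month change as secondary.

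The cost is one chairside reading during surgery that is already planned, plus revised analysis text, with no extra visit or imaging. The drawback is that a chairside baseline and CBCT follow-up are different methods. The report should state that measurement error and read small changes in its light.

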### Radiograph Interpretation

All recorded radiographs (OPG, IOPAR, and CBCT) will be assessed by 2 investigators. Both the investigators are trained professionals in the field of prosthodontics and oral and maxillofacial surgery, respectively, and have experience of more than 15 years in patient rehabilitation. Before beginning the study, both investigators will be trained in interpreting CBCTs of previously recorded cases that are not related to the current study to practice consistent reading. Each investigator will reassess the recorded radiographs after 1 month to determine intraobserver variability. The findings of the 2 investigators will also be subjected to evaluation of interobserver variability.

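### Kappa is named without weighting or restriction for radiographic reader agreement, although the readings include quantitative marginal bone levels, for which unweighted Kappa is misleading

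*Protocol article*

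**What the plan says.** The Results section of the protocol article describes two kinds of radiographic reading. The first is a measurement: "CBCTs recorded after dental implant placement will be quantitatively compared to determine the presence of any significant variation in the marginal bone levels". The second is a judgement of presence or absence: "Qualitative assessments of the radiographs will be done to determine the presence of periapical pathology and any other abnormal radiographic findings". The next sentence names the agreement statistic: "Intra- and inter-observer variability in radiographic assessments will be evaluated by using the Kappa statistic". It mentions no weights, no grouping of bone levels into categories and no limit to the second kind of reading.

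The Radiograph Interpretation section sets up the data for this. On the scope of the reading it says: "All recorded radiographs (OPG, IOPAR, and CBCT) will be assessed by 2 investigators". On repeat reading by the same person it says: "Each investigator will reassess the recorded radiographs after 1 month to determine intraobserver variability". On the comparison between readers it adds: "The findings of the 2 investigators will also be subjected to evaluation of interobserver variability". Nothing there limits the agreement check to one type of finding.

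For the comparison of the two follow-up visits, the plan names the *t* test and continues: "tests, Wilcoxon tests, and chi-square tests will be utilized to determine statistical significance of clinical and radiological parameters assessed at 3 months and 9 months". At least some of these parameters are therefore to be analysed as numerical values.

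**The concern.** Marginal bone level is the only quantitative radiographic measure that the statistical paragraph names, and it is a length. Ordinary Kappa is designed for categories: two readings either fall in the same category or they do not. Applied to lengths, it scores a difference of one recording unit and a difference of 2 mm alike, as failures to agree. A finer recording unit also produces fewer exact matches, so Kappa falls although the readers are no worse.

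What is at stake is the reported reliability of the bone levels. A low Kappa could make good readers look unreliable. Nor could it show a reader of the eventual paper whether two investigators differ trivially or grossly. To judge whether a change from 3 to 9 months exceeds reader error, one needs that error in mm, and Kappa does not give it.

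**Working it through.** The plan states no figure for reader agreement, so there is none to reproduce. The checks below show how Kappa behaves on readings of this type. The 30 implants come from the Sample Size Calculation section. All reader and bone-level values are assumptions.

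**Check 1, constant offset (exact).** Kappa = (p_o − p_e)/(1 − p_e), where p_o is observed and p_e is chance agreement. Let reader A record 30 values spaced 0.1 mm apart, and let reader B record each with a constant offset.

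- Offset 0.1 mm: p_o = 0. The readers share 29 values, so p_e = 29/900 = 0.0322. Kappa = −0.0322/0.9678 = −0.03.
- Offset 2 mm: p_o = 0. They share 10 values, so p_e = 10/900 = 0.0111. Kappa = −0.0111/0.9889 = −0.01.

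The two-way absolute-agreement ICC for two readers is (MS_R − MS_E)/(MS_R + MS_E + 2(MS_C − MS_E)/n), where R denotes implants, C readers and E residual. Here MS_E = 0 and MS_R = 2 × 22.475/29 = 1.55.

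- Offset 0.1 mm: MS_C = 30 × 2 × 0.05² = 0.15. ICC = 1.55/(1.55 + 0.01) = 0.99.
- Offset 2 mm: MS_C = 30 × 2 × 1² = 60. ICC = 1.55/(1.55 + 4) = 0.28.

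Kappa is near zero in both cases, while the ICC separates them.

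**Check 2, random reader error (simulation).** Two readers measure 30 implants, with 500 runs per setting and no systematic offset. Each cell gives the mean at a recording unit of 0.1 mm / 0.01 mm.

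| Between-implant SD (mm) | Reader-error SD (mm) | Unweighted Kappa | Quadratic-weighted Kappa | ICC |
|---|---|---|---|---|
| 0.5 | 0.1 | 0.219 / 0.022 | 0.954 / 0.957 | 0.956 / 0.959 |
| 0.5 | 0.2 | 0.087 / 0.008 | 0.845 / 0.854 | 0.849 / 0.858 |
| 0.8 | 0.1 | 0.242 / 0.021 | 0.982 / 0.983 | 0.983 / 0.984 |
| 0.8 | 0.2 | 0.100 / 0.010 | 0.934 / 0.936 | 0.936 / 0.938 |

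The ICC column agrees with SD²/(SD² + error²). For the first row this is 0.25/0.26 = 0.96, and for the second 0.25/0.29 = 0.86. Moving from a 0.1 mm to a 0.01 mm unit cuts unweighted Kappa about tenfold and leaves the ICC almost unchanged.

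With a systematic offset of 0.5 mm added to one reader, the ICC falls to 0.59 to 0.82, while unweighted Kappa lies between −0.04 and 0.00.

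**Check 3, rare categorical findings.** Kappa suits these, but should not stand alone. Suppose one reading in 30 is discordant and 29 are agreed negatives (an assumed count). Then p_o = 29/30 = 0.967 and p_e = 29/30 × 1 + 1/30 × 0 = 0.967. Kappa is 0 despite 97% agreement, so raw percent agreement is worth reporting beside it.

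**Check 4, what is not touched.** The sample size follows from 1.96² × 0.95 × 0.05/0.08² = 28.5, in line with the stated 28, and 28/0.95 rounds up to 30. No reader-agreement quantity enters. The comparison of 3 and 9 months uses the readings themselves, not the agreement coefficient.

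**The case against.** The strongest reply is that the Kappa sentence directly follows the one on qualitative assessments and repeats its noun, so Kappa may be meant only for the present/absent findings. Kappa is suitable there, and a condensed article may leave the statistic for bone levels to a fuller document. This reading is possible, and a reader who infers that Kappa is expressly fixed for every radiographic assessment goes further than the text. But the sentence is not limited in this way, and the Radiograph Interpretation section puts all radiographs and both investigators' findings into the agreement check without regard to type. The ambiguity needs correcting on either reading.

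Second, weighted Kappa is also a Kappa. With quadratic weights it came close to the ICC in the simulation (0.58 to 0.98 against 0.59 to 0.98, including the settings with offset). That stands: it would be wrong to call every form of Kappa invalid for these data. The article states no weights, however, and a weighted Kappa still gives no error in mm.

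Third, the patient record sheet is not shown. If it also grades bone loss into categories, Kappa on those grades would be legitimate. That also stands, but it would not cover the bone levels that the article says are "CBCTs recorded after dental implant placement will be quantitatively compared".

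Fourth, it is tempting to say that the measurement error would be unavailable. The documents do not support this. If bone levels are recorded in mm, the planned duplicate and repeat readings allow it to be calculated whatever coefficient is named.

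**Conclusion.** The point holds as a matter of how reader reliability is reported. Followed as written, with ordinary unweighted Kappa on millimetre readings, the plan would give a coefficient of about 0.01 to 0.24 where the ICC is 0.85 to 0.98. That coefficient could not tell a 0.1 mm from a 2 mm reader offset. The ranges rest on the assumed SDs, error sizes and recording units above. They illustrate a property of the statistic and do not predict this trial's values. The constant-offset check needs no assumption about random error.

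A reader might infer that the radiographic result itself is compromised, or that marginal bone level is the main radiographic outcome. The documents support neither. They do not rank the radiographic outcomes, and no efficacy estimate, test or sample size depends on the agreement statistic. Confidence that unweighted Kappa is unsuitable for bone levels is high. Confidence that it was intended for them is moderate, because of where the sentence stands.

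**What to change.** Split the agreement sentence in the Results section by type of reading.

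- **Categorical findings** (periapical pathology, other abnormalities): Kappa for inter- and intra-observer agreement, with raw percent agreement beside it.
- **Marginal bone level:** two-way absolute-agreement ICC with 95% CI, plus Bland-Altman bias and limits of agreement in mm, for both inter- and intra-observer data.

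If bone loss is also graded, state the grades and use Kappa for the grades only, saying whether it is weighted. Analysing the mean of the two readers' bone levels is an optional extra and does not follow from this point.

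The cost is a change of analysis wording. The second reader and the 1-month repeat reading are already planned, so no new images, visits or patients are needed.

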### Sample Size Calculation

A recent study showed a success rate of 95% for dental implant–based treatment in cleft patients [10]. With a type I error of 5%, confidence interval of 95%, and 8% margin of error, a sample size of 28 dental implants was obtained. Considering 5% loss to follow-up, an additional 2 dental implants will be placed. Thus, a total sample size of 30 dental implants in sequential patients will be considered for the proposed study.

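### Kappa is the only agreement statistic named for yes/no radiographic findings; if those findings are rare, it can be undefined, zero or negative at about 30 images even though the readers agree on about 95% of them

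*Protocol article*

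**What the plan says.** Under Radiograph Interpretation, "All recorded radiographs (OPG, IOPAR, and CBCT) will be assessed by 2 investigators", and "Each investigator will reassess the recorded radiographs after 1 month to determine intraobserver variability". Inter-observer variability is to be evaluated as well. Both are therefore planned results of the trial.

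The analysis text under Results describes two kinds of reading. Marginal bone levels on CBCT are compared quantitatively. Separately, "Qualitative assessments of the radiographs will be done to determine the presence of periapical pathology and any other abnormal radiographic findings". It then fixes the agreement measure for all of them: "Intra- and inter-observer variability in radiographic assessments will be evaluated by using the Kappa statistic". No other agreement measure is named.

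The number of images follows from two further statements. Under Sample Size Calculation, "a total sample size of 30 dental implants in sequential patients will be considered"; under Follow-Up, "All patients will undergo 2 clinical follow ups, 3 months and 9 months after implant placement". That gives about 30 post-implant images per visit and image type, or about 60 over both visits. The article does not say how common the abnormal findings are expected to be, which images enter each Kappa, or whether visits are pooled.

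**The concern.** Presence or absence of a finding is categorical, so Kappa looks like the natural choice. It corrects raw agreement for the agreement expected by chance from the readers' marginal totals. When nearly every image is read as normal, that chance-expected agreement is close to 1, the denominator of Kappa is close to 0, and one or two images decide the result. If neither reader sees any abnormality, Kappa does not exist.

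The aim of the trial is clinical and radiographic success, and the reader-agreement result is meant to show that the radiographic readings can be trusted. A reported Kappa of 0, or no value at all, would leave that question open even where the readers disagreed on a single image. Choosing another index after seeing such a result would look selective.

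This point is separate from whether Kappa suits millimetre bone levels. It concerns the categorical readings for which Kappa would be kept.

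**Working it through.** **Inputs from the article.** 30 implants; two follow-up visits; two readers; Kappa as the only named agreement statistic; an earlier study's 95% treatment success rate with an 8% margin of error (Sample Size Calculation).

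**The plan's own figure.** n = 1.96² × 0.95 × 0.05 / 0.08² = 28.5, stated as 28; 28 / 0.95 = 29.5, giving 30. The planned size reproduces to rounding. The article states no figure for reader agreement, so there is none to reproduce.

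**Step 1: the mechanism, without assumptions.** For a 2x2 table with a = both positive, b and c = discordant, d = both negative, and n images:

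- observed agreement: po = (a + d) / n
- chance agreement: pe = [(a + b)(a + c) + (c + d)(b + d)] / n²
- Kappa = (po − pe) / (1 − pe)

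At n = 30:

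| a, b, c, d | Raw agreement | pe | Kappa |
|---|---|---|---|
| 0, 0, 0, 30 | 100% | 900/900 | 0/0, undefined |
| 0, 1, 0, 29 | 96.7% | 870/900 | 0 |
| 0, 1, 1, 28 | 93.3% | 842/900 | −2/58 = −0.03 |
| 1, 1, 0, 28 | 96.7% | 814/900 | 56/86 = 0.65 |

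Rows two and four have the same raw agreement. One jointly called positive moves Kappa from 0 to 0.65.

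**Step 2: how often this happens.** This needs assumptions that the article does not supply: a prevalence π, and two readers with conditionally independent errors, sensitivity 0.90 and specificity 0.98. The cell probabilities are:

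- both positive: 0.90²π + 0.02²(1 − π)
- each discordant cell: 0.90 × 0.10 × π + 0.98 × 0.02 × (1 − π)
- both negative: 0.10²π + 0.98²(1 − π)

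At π = 0.05 these are 0.0409, 0.0231 (twice) and 0.9129, so expected agreement is 0.0409 + 0.9129 = 95.4%. The chance that both readers call all 30 images normal is 0.9129³⁰ = 6.5%.

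Summing exactly over all possible 2x2 tables, and treating images as independent:

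| Prevalence | Agreement | n = 30: undefined | n = 30: zero or negative | n = 30: total | n = 60: total |
|---|---|---|---|---|---|
| 2% | 95.8% | 16.3% | 44.2% | 61% | 37% |
| 5% | 95.4% | 6.5% | 22.1% | 29% | 8% |
| 10% | 94.7% | 1.3% | 6.5% | 8% | 0.6% |
| 20% | 93.3% | under 0.1% | 0.5% | 0.5% | 0% |

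At n = 30 and 5% prevalence, the median of the defined Kappas is 0.63, with a 95% range of −0.05 to 1.00. At 50% prevalence the same readers agree less often (89%), yet the median Kappa is 0.79 (0.52 to 1.00).

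**Step 3: sensitivity to the reader assumptions.** With sensitivity 0.80 to 0.95 and specificity 0.975 to 0.98, the total at n = 30 is 57–67% at 2% prevalence, 25–37% at 5%, 6–14% at 10%, and 2% or less at 20%. If raw agreement is instead fixed at 95% and each reader calls 5% of images positive, the total is 47% at n = 30 and 22% at n = 60.

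**Step 4: what survives when Kappa fails.** Wilson 95% intervals for raw agreement at n = 30: 30 of 30 gives 88.6–100%; 29 of 30 gives 83.3–99.4%; 28 of 30 gives 78.7–98.2%. Gwet's AC1 is 0.97 for the table 0, 1, 0, 29 and 0.93 for 0, 1, 1, 28.

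Positive specific agreement, 2a / (2a + b + c), does not help. It is 0/0 in the first row of Step 1 and 0 in the next two. A bootstrap interval for raw agreement has zero width whenever no image is discordant, which at 5% prevalence and n = 30 happens in (1 − 2 × 0.0231)³⁰ = 24% of samples.

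**The case against.** **Rarity is assumed.** This stands. The 95% in the sample size section is a treatment success rate from an earlier study, not a rate of radiographic abnormality. The category of other abnormal findings is open-ended and could be common in grafted cleft sites. A reader might infer that the plan itself implies 0 to 3 abnormal images in 30; the article does not say so. At 10% prevalence the problem is modest, and at 20% it is nearly absent.

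**The unit is the radiograph, not the implant.** This stands in part. All radiographs are read and there are two follow-up visits, so a Kappa could rest on about 60 images. That cuts the failure share at 5% from 29% to 8%, but at 2% it is still 37%. The article does not say that visits are pooled.

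**Independent errors are a poor model for re-reading.** This stands. The same reader's errors after one month are likely to be correlated, so the Step 2 percentages describe inter-observer agreement only. The Step 1 arithmetic applies to both.

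**Kappa is conventional, and extra figures belong in an analysis plan.** Kappa is not an error for categorical data, and the article does not exclude reporting raw agreement. But it names one statistic for all radiographic variability, and that stated choice can be judged.

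**Stronger readings.** One might infer that Kappa is the trial's only safeguard for the radiographic readings. It is not: Radiograph Interpretation also provides experienced readers, training on unrelated cases and repeat reading. One might also infer that the success definition is compromised. The article does not show whether periapical pathology forms part of it, because the criteria are in a cited consensus and the record sheet appendix.

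**Conclusion.** The point holds in a limited form. Kappa alone is a fragile summary of agreement on yes/no radiographic findings in a trial of this size, if those findings occur in about 5% of images or fewer. Under the stated reader assumptions, per-visit Kappa would then be undefined, zero or negative in roughly three samples in ten at 5% and six in ten at 2%, despite about 95% raw agreement. Pooling both visits largely removes the problem at 5% but not at 2%.

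The size of the problem depends on a prevalence that the article does not give. What needs no assumption is that zero or one abnormal call in 30 images yields no Kappa, or a Kappa of 0, unless both readers make that call on the same image. The consequence is confined to a secondary reliability result; the implant success estimate and the conduct of the trial are unaffected. The case for acting rests on the very low cost.

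**What to change.** In the analysis text under Results, for yes/no radiographic findings:

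- Report the 2x2 counts and raw agreement with a Wilson or exact 95% confidence interval beside Kappa, for both intra- and inter-observer readings.
- Pool the two follow-up visits for the agreement analysis, and state which images enter each Kappa. Two images of the same implant are not fully independent, so the pooled interval should be described as approximate.
- Optionally add a prevalence-robust index such as Gwet's AC1, always read with the 2x2 counts, because it can be high when the readers never jointly call a positive.
- Do not rely on positive specific agreement when there are no positives, or on a bootstrap interval when there are no discordant images.

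No index makes up for having few abnormal images; the counts and the interval let the reader see that limit. The cost is a sentence or two in the analysis section and a few extra reported figures. No new readings are needed.
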